### 2.1. Trial Design and Setting

This pragmatic study is designed as a single-blinded, randomized, three-treatment-arm (1:1:1) study involving chronic outpatients from neurorehabilitation units of 10 FIT4TeleNEURO Centers: (1) IRCCS Fondazione Don Carlo Gnocchi ONLUS, Milano (MI); (2) IRCCS Fondazione Don Carlo Gnocchi ONLUS, Roma (RO); (3) IRCCS Fondazione Mondino, Pavia (PV); (4) IRCCS Istituti Clinici Scientifici Maugeri, Bari (BA); (5) IRCCS Istituti Clinici Scientifici Maugeri, Milano (MI); (6) IRCCS Istituti Clinici Scientifici Maugeri, Pavia (PV); (7) IRCCS Istituti Clinici Scientifici Maugeri, Montescano (PV); (8) IRCCS Istituti Clinici Scientifici Maugeri, Telese (BN); (9) Università di Modena e Reggio Emilia, Modena (MO); and (10) Ospedale Valduce, Centro di Riabilitazione “Villa Beretta”, Como (CO).

Following enrollment and the baseline assessment, each participant will be randomly assigned into one of the following three groups, with an allocation ratio of 1:1:1: (1) telerehabilitation single approach (TRsA, experimental group); (2) telerehabilitation combined approach (TRcA, experimental group); or (3) conventional educational treatment (CeT, placebo comparator).

Randomization will be stratified based on both the clinical center and the clinical conditions (MS, PD). Primary and secondary outcome measures will be collected at baseline (T0), post-intervention (T1, 5 weeks after baseline), and at follow-up (T2, 12 weeks after treatment completion). The trial work plan is shown in Figure 2.

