### 2.2. Sample Size

The sample size was determined a priori using G*Power 3 software, based on previously published preliminary data [30] related to the study’s primary outcome, the Mini-Best test. Assuming a minimal clinically important difference (MCID) of 3 points (ds group 1 = 5.75, ds_group 2 = 5.98), a statistical power of 80% (type I error rate of 0.05), and an allocation ratio of 1:1:1, 48 subjects per group are required. These groups include TR with single approach (TRsA) and the control group. A third group (TR with combined approach, TRcA) of 48 subjects will be recruited to assess whether a neuromotor rehabilitation program combining two approaches (task-oriented and impairment-oriented) is superior to the control group and differs from the TRsA group in secondary outcomes. The study will recruit 144 patients with Parkinson’s disease and 144 patients with multiple sclerosis. To account for a potential 5% drop-out rate per pathology group, a total of 300 subjects will be enrolled.

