### 2.3. Study Population, Recruitment, and Randomization

Based on the sample size calculation, the trial intends to recruit 300 individuals with CND, comprising 150 diagnosed with PD and 150 with MS. Recruitment will be competitive across participating centers. Eligible patients who meet all inclusion criteria (outlined in the section below) will be randomized through a web-based allocation concealment method, using a computer algorithm created by an independent statistician. Stratified randomization will be utilized to prevent imbalances between treatment groups. Participants will be stratified according to their clinical center and condition (MS, PD) and then randomly assigned (1:1:1) to one of the experimental groups (TRsA or TRcA) or the control group (CeT) (Figure 3). The intervention will not be blinded for either clinicians or patients due to its nature. However, clinical endpoints and data collection from clinical/psychological questionnaires will be blinded for examiners/assessors. The statistician conducting the data analysis will also be blinded to group allocation.

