### 2.8. Statistical Analysis

Descriptive statistics will be employed to characterize the sample, with mean and standard deviation (SD) reported for normally distributed variables, and median and interquartile range (IQR) for non-normally distributed variables.

Data analysis will follow the modified intention-to-treat (mITT) principle [70], ensuring that all participants with available baseline data are included in the analysis. Missing data will be addressed using multiple imputation techniques to minimize bias and enhance the robustness of findings. However, we will also conduct a complete records analysis as a comparison. To test the effect of the treatment on the outcome measures, generalized linear mixed models (GLMMs) [71] will be employed. The model will evaluate changes over time (T0, T1, T2) and differences between groups (TRsA, TRcA, CeT), with outcome scores serving as dependent variables. Independent variables (fixed factors) will include time, group, and the interaction term (time × group) to capture both main effects and interaction effects. 

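### Randomization is stratified by center and condition, but the listed model terms include neither, which can make standard errors too large

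*Protocol article*

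**What the plan says.** Section 2.1 of the protocol article states: "Randomization will be stratified based on both the clinical center and the clinical conditions (MS, PD"). It lists 10 centers. Section 2.3 repeats the scheme ("Participants will be stratified according to their clinical center and condition (MS, PD") and gives the purpose: "Stratified randomization will be utilized to prevent imbalances between treatment groups".

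For the analysis, Section 2.8 says that "generalized linear mixed models (GLMMs) [71] will be employed". The response includes the baseline score: "The model will evaluate changes over time (T0, T1, T2) and differences between groups (TRsA, TRcA, CeT), with outcome scores serving as dependent variables". The fixed part is then listed: "Independent variables (fixed factors) will include time, group, and the interaction term (time × group) to capture both main effects and interaction effects". No random effect is named, and the section does not say whether PD and MS are analyzed together or separately.

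Two other places bear on this. Section 2.2 sizes each disease separately, with 48 per arm and 144 patients per disease. The last paragraph of the Introduction names a secondary aim of comparing the effect of the interventions between the MS and PD cohorts.

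**The concern.** Stratified allocation balances the arms on center and condition, so variation between strata is largely removed from the true sampling error of the treatment comparison. A model without these factors leaves that variation in its estimated error. The estimate stays unbiased, but its reported standard error is larger than its real one, intervals over-cover, and precision that the design has already secured is lost.

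The gap lies in the text itself and is not only a matter of brevity: the article sets out its list of fixed factors, and that list does not follow the design. If the diseases are pooled, the same list also contains no term from which the PD versus MS difference in effect could be estimated.

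**Working it through.** **The plan's own figure.** Section 2.2 gives "Assuming a minimal clinically important difference (MCID) of 3 points (ds group 1 = 5.75, ds_group 2 = 5.98") and "a statistical power of 80% (type I error rate of 0.05").
- Pooled SD = √((5.75² + 5.98²)/2) = 5.866; standardized difference = 3/5.866 = 0.511.
- A one-sided 0.05 test with 80% power needs 48 per group, which matches the article. A two-sided test needs 61.
- Two-sided power (normal approximation) is 70.7% at 48 per arm (one disease) and 94.3% at 96 per arm (both diseases pooled). The t-test gives 69.8% and 94.1%.

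**Comparison of two arms at one visit.** Let R² be the share of outcome variance explained by the strata, with near-exact balance within strata. R² is not in the article, so 5 to 15% is an assumed range.
- Unadjusted SE = 5.866 × √(2/n): 1.197 at n = 48 and 0.847 at n = 96.
- Real SE = unadjusted SE × √(1 − R²), so the SE is overstated by the factor 1/√(1 − R²).
- Real two-sided type I error = 2 × (1 − Φ(1.96/√(1 − R²))).
- Power unadjusted = Φ((3 − 1.96 × unadjusted SE)/real SE); power adjusted = Φ(3/real SE − 1.96).

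Example, n = 48 and R² = 10%: real SE = 1.197 × 0.949 = 1.136. Unadjusted power = Φ((3 − 2.347)/1.136) = Φ(0.575) = 71.7%. Adjusted power = Φ(2.641 − 1.96) = Φ(0.681) = 75.2%.

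| R² | SE ratio | Real type I error | Power at 48/arm, unadjusted vs adjusted | Power at 96/arm, unadjusted vs adjusted |
|---|---|---|---|---|
| 5% | 1.026 | 0.044 | 71.2 vs 72.9% | 94.8 vs 95.3% |
| 10% | 1.054 | 0.039 | 71.7 vs 75.2% | 95.2 vs 96.2% |
| 15% | 1.085 | 0.034 | 72.3 vs 77.6% | 95.7 vs 97.0% |

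The 48-per-arm column describes a single disease, so there R² is the share due to center alone. Pooled, even R² = 30% costs only 1.8 points (97.1 vs 98.9%).

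**Time × group contrast.** Because T0 is part of the response, a stratum effect that is the same at every visit cancels from the change. This was checked on simulated data: 300 patients, 20 strata of 15, three visits, a patient random intercept (SD 4.5) and residual SD 3.7, all assumed.
- *Stratum effects constant over time* (center SD 2, condition difference 3), one data set. The SE of the T1 contrast is 0.7254 without strata, 0.7254 with strata as main effects, and 0.7259 with strata × time. The SE of a single-visit group difference does fall, from 0.9513 to 0.8103.
- *Stratum effects that change over time* (center SD 2 points, condition shift 2 points). In one data set the SE is 0.7821 without strata, 0.7821 with main effects only, and 0.7475 with strata × time. Averaged over simulations it is 0.783 without and 0.742 with strata × time (ratio 1.055), and power for a 1.5-point effect is 48% versus 53%.

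So main effects alone do not help the change contrast. The interactions with time do, and only when the strata really differ in their course.

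**The case against.** A reader might infer that the model certainly omits both factors and certainly loses power. The text does not go that far.
- Section 2.8 specifies a mixed model without naming its random effects, so a center effect is neither stated nor excluded. A center intercept alone would still not sharpen the change contrast.
- The sizing in Section 2.2 is compatible with separate analyses of PD and MS. Condition is then constant and rightly absent; center would still be missing from the listed terms.
- For the time × group contrast, harm requires strata that differ in their course over time, and the article gives no figure for that.

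A reader might also infer that the trial already falls short of a stated two-sided power. Section 2.2 states no sidedness. Two-sided power at its figures is about 70% per disease but about 94% pooled, and condition can be an omitted factor only in the pooled case, where there is ample power to spare.

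Nor can the two telerehabilitation systems in Section 2.5 be cited as a source of center variation. The article does not tie system to center and says that the exercises were harmonized across them.

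Finally, the error is on the conservative side. All of these limits stand. What remains is that the one list of fixed factors given does not match the stated design.

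**Conclusion.** The point holds as a conditional loss of precision. The fixed factors listed in Section 2.8 leave out both stratification factors. If these explain 5 to 15% of the variance of change, or of the score at a visit where arms are compared, standard errors are about 3 to 8% too wide and a nominal 5% two-sided test runs at about 4.4 to 3.4%.

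The loss is near zero for the time × group contrast if stratum effects are constant over time and a patient intercept is fitted. The power loss is about 2 to 5 points at 48 per arm if center alone explains 5 to 15%, and about 1 point at 96 per arm. These sizes rest on the assumed R² and on good balance within strata; small strata under competitive recruitment would reduce the balance.

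There is no bias and no inflated false-positive risk, so this should be corrected but does not threaten validity. If the diseases are pooled, the listed terms also cannot answer the Introduction's PD versus MS question, whatever R² is.

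**What to change.** In Section 2.8:
- State whether PD and MS are pooled or analyzed separately, and name the random effects, including a patient effect.
- If pooled, add condition and condition × time as fixed effects to the primary model. If separate, condition drops out.
- Add center and center × time in one form decided in advance (fixed or random, not left open). Name a fallback if the model does not converge, for example center without its time interaction.
- Use the same factors in the multiple-imputation model.
- If pooled, add a group × condition × time term in a secondary model for the PD versus MS aim, because condition × time alone does not estimate a difference in treatment effect.

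The cost is a few sentences and no new data, since both factors are already recorded for randomization. With center as a fixed effect, the pooled primary model gains at most 1 + 2 + 9 + 18 = 30 parameters for 300 patients with three visits each. The 10 × 2 strata average 15 patients, about 5 per arm, and some will be smaller, which is why the fallback must be named beforehand.

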Technological advancements in healthcare, as highlighted by Topol [18], provide an opportunity to transform the healthcare system and care delivery, with digital medicine and telemedicine playing a pivotal role in this transition. Among telemedicine applications, telerehabilitation (TR) has emerged as a promising approach for delivering integrated, continuous care for individuals with chronic neurological disabilities from the earliest stages [19,20,21]. Research has demonstrated the feasibility of TR interventions for various CNDs, including MS [22,23,24,25,26,27,28] and PD [29,30,31,32,33,34,35,36,37], as well as conditions within the Alzheimer’s disease continuum [38,39]. These studies suggest that TR can achieve clinical outcomes and medical benefits comparable to traditional rehabilitation methods. However, limitations such as heterogeneous intervention protocols, small sample sizes, and a lack of standardized approaches remain challenges.

Task-oriented training is the predominant rehabilitation approach employed in the early stages of CNDs to enhance functional mobility and physical capacity. Additionally, growing evidence suggests that integrating task-oriented strategies with impairment-oriented activities may result in superior outcomes [40,41,42]. However, there remains a lack of standardized approaches in both TR and conventional care, underscoring the urgent need to establish consistent and evidence-based protocols.

The FIT4TeleNEURO study aims to implement a harmonized, multicenter TR protocol specifically designed for the early stages of PD and MS to address gait and balance difficulties at home. The study will evaluate whether this TR protocol is acceptable and effective through a pragmatic trial design, assessing its superiority over conventional care in early rehabilitative management. Furthermore, secondary objectives include examining the specific effects of rehabilitative strategies by comparing task-oriented and combined task- and impairment-oriented approaches on motor, cognitive, and quality-of-life outcomes, as well as investigating the differential impact of these digital interventions on MS and PD cohorts.

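### The sample size is set within each disease, but the listed model has no disease term: the 80% power is tied to no stated test, and the PD-versus-MS objective gets no estimate

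*Protocol article*

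**What the plan says.** Three places in the protocol article bear on this.

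- **Section 2.2 (Sample Size).** The planning inputs are: "Assuming a minimal clinically important difference (MCID) of 3 points (ds group 1 = 5.75, ds_group 2 = 5.98"), with "a statistical power of 80% (type I error rate of 0.05"). The result is "an allocation ratio of 1:1:1, 48 subjects per group are required". The comparison sized is TRsA against control: "These groups include TR with single approach (TRsA) and the control group". The figure is then used twice: "The study will recruit 144 patients with Parkinson’s disease and 144 patients with multiple sclerosis". Since 144 = 3 × 48, each disease receives a full three-arm sample. Drop-out is also allowed for by disease.
- **Sections 2.1 and 2.3.** Randomisation is stratified by centre and by condition (MS, PD).
- **Section 2.8 (Statistical Analysis).** Generalized linear mixed models will be used. The model terms are given as: "Independent variables (fixed factors) will include time, group, and the interaction term (time × group"). Disease is not among them. The section says neither that the diseases are pooled nor that they are analysed apart.

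The Introduction gives as one secondary objective "investigating the differential impact of these digital interventions on MS and PD cohorts".

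**The concern.** The sample size and the analysis do not visibly describe the same test. Section 2.2 makes a within-disease power statement, while Section 2.8 describes a model in which disease does not appear. A reader cannot tell whether the primary result will be one effect over both diseases or one effect in each, and the power differs between the two.

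A named objective also has no matching quantity in the analysis. A single model without disease returns an average over PD and MS. Two separate models return two effects but no comparison between them, and they invite the error of treating significance in one disease and not in the other as evidence that the diseases differ.

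If the choice between pooled and per-disease analysis stays open until data are seen, it can be made in the light of the results.

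**Working it through.** **Inputs (Section 2.2).** Difference 3 points; SDs 5.75 and 5.98; type I error 0.05, sidedness not stated; 48 per arm in each disease. Pooling the diseases gives 2 × 48 = 96 per arm.

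Common SD = √[(5.75² + 5.98²)/2] = 5.866; standardised difference = 3/5.866 = 0.511.

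**Step 1: reproduce the plan's figure.** Two-sample t-test, noncentral t, with noncentrality = 3 / (5.866 × √(2/n)).

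- n = 48: 3 / 1.197 = 2.505. Power is 80.0% one-sided and 69.8% two-sided.
- The smallest n for 80% power is 48 one-sided and 61 two-sided.

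So 48 reproduces exactly, as a one-sided 5% test within one disease.

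**Step 2: one model on all participants.** n = 96: 3 / (5.866 × √(2/96)) = 3 / 0.847 = 3.543.

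| Reading of Section 2.8 | Per arm | Power, one-sided | Power, two-sided |
|---|---|---|---|
| Fitted within one disease | 48 | 80.0% | 69.8% |
| One model, both diseases | 96 | 97.0% | 94.1% |

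The pooled row assumes the same 3-point effect in both diseases. If the effect were 3 points in one disease and 0 in the other, the pooled effect would be 1.5 points, with power of 42.2% two-sided (54.8% one-sided). The resulting estimate would describe neither disease.

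**Step 3: the PD–MS contrast.** This is the treatment effect in PD minus that in MS, with 48 in each of four cells.

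- Standard error = 5.866 × √(4/48) = 1.693, twice the pooled standard error of 0.847.
- Power for a 3-point difference in effect (normal approximation), two-sided: Φ(3/1.693 − 1.960) = Φ(−0.188) = 42.5%. One-sided: Φ(3/1.693 − 1.645) = 55.0%.
- Difference detectable with 80% power: (1.960 + 0.842) × 1.693 = 4.7 points two-sided; (1.645 + 0.842) × 1.693 = 4.2 points one-sided.

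**Step 4: sensitivity to the outcome SD.** Section 2.2 does not say whether its SDs are of scores or of change. If they are of scores and change is analysed, the SD of change is 5.866 × √[2(1 − r)], where r is the between-visit correlation, which is not given. Taking r as an assumption, two-sided power for the 3-point contrast is:

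| r (assumed) | SD of change | Standard error | Power |
|---|---|---|---|
| 0.3 | 6.94 | 2.00 | about 32% |
| 0.5 | 5.87 | 1.69 | about 43% |
| 0.8 | 3.71 | 1.07 | about 80% |

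The power of the two main readings would shift with r in the same way.

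**The case against.** The strongest reply has four parts.

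1. **Pooling is not stated.** A reader might infer that the diseases are pooled and that the 80% therefore fits no planned test. The documents do not support that. Section 2.8 speaks of models in the plural before describing one, and the sizing by disease fits separate models well. On that reading 48 per arm does give 80%, provided the test is one-sided, and the stated hypothesis is superiority. This stands: the defect is an unstated analysis population and sidedness, not a proven pooled analysis.
2. **The trial can answer the PD–MS question.** A reader might infer that the objective is out of reach. It is not. Randomisation is stratified by disease with about 150 patients in each, so the contrast can be estimated without any design change. What lacks it is the model as listed. Nor does the article claim that this contrast is powered, so low power contradicts nothing.
3. **Pooling does not cost power.** Under a common effect, power rises above 80%. This stands; the issue is what the averaged effect means, not a weaker primary comparison.
4. **A condensed article may leave this to the analysis plan.** The list of factors need not be exhaustive, and an unseen plan may add the interaction. This stands in part. The article does, however, go as far as listing the fixed factors, and the list omits both a stratification factor and the term that a stated objective needs. The mismatch with Section 2.2 is visible in the article itself.

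**Conclusion.** The point holds as a mismatch between sections. The sample size is per disease. The listed model has no disease term, and the article does not say how the diseases enter the analysis. The 80% does not describe one model on all participants (94% two-sided, 97% one-sided), and it describes a per-disease test only if that test is one-sided (70% two-sided). On both readings, the listed terms yield no estimate of how the effect differs between MS and PD.

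The figures rest on a simple two-group comparison, a 3-point effect, an SD of 5.87 taken as equal in PD and MS and as that of the analysed outcome, and 48 completers per arm and disease. The figure of about 43% for the contrast is the most sensitive to the SD assumption.

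The primary comparison is not endangered under a common effect. A reader might also conclude that the pooled test ought to be primary, but the per-disease sizing gives no support for preferring it. That choice belongs to the sponsor and only needs to be declared. Correcting this is a cheap improvement to make before analysis.

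**What to change.** - Add disease (the stratification factor) and the disease × group × time interaction, with its lower-order terms, to the model in Section 2.8.
- For the differential-impact objective, report the treatment effect in PD, in MS, and their difference with a 95% CI. Do not infer a difference from separate p-values.
- State that this contrast is estimated, not powered, and give its approximate precision together with the SD and between-visit correlation assumed.
- State whether the primary test is pooled and disease-adjusted or per disease, and restate the power and sidedness in Section 2.2 for that test.

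Cost: revised wording, slightly more analysis and one more model. No additional patients and no change to randomisation or assessments.

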## 3. Discussion

The increasing demand for rehabilitation among individuals with CNDs underscores the critical need for innovative digital solutions to enhance accessibility and optimize clinical, functional, and quality-of-life outcomes. People with PD and MS are particularly reliant on rehabilitative care due to their progressive neurodegenerative nature and share common rehabilitative goals, including improving functional mobility and physical capacity. Evidence demonstrates that early, intensive rehabilitation enhances exercise tolerance, walking ability, and balance while mitigating fall risks—a critical concern for these populations [7,8,13]. However, barriers such as limited access to timely and intensive interventions persist. Digital technologies, being easily transportable, facilitate their implementation across diverse settings, including patients’ homes or other non-hospital environments. Moreover, TR is recognized as a powerful tool to strengthen primary healthcare rehabilitation services, extending access to care and overcoming logistical barriers [72].

This pragmatic trial aims to assess the effectiveness of early rehabilitative interventions delivered through a standardized TR protocol for individuals with PD and MS. Effectiveness will be evaluated not only via performance-based tests (e.g., MINI-BESTest, mDGI, …) but also by integrating patient-reported outcome measures (PROMs) such as WHODAS 2.0 and FSS questionnaire. PROMs provide invaluable insights into patients’ recovery processes, contributing to a comprehensive understanding of therapeutic success [73]. Additionally, data collected from this multicenter cohort, supported by a substantial sample size, will provide critical insights into preceding considerations, multidisciplinary assessment, and transferability evaluation. These findings will be pivotal for conducting future cost-effectiveness and acceptability conducted in accordance with the Model for Assessment of Telemedicine (MAST) framework, which is grounded in the EUnetHTA model [74].

We anticipate that TR protocols will be both usable and acceptable for individuals with MS and PD, and this rehabilitative method is expected to result in significant improvements in static and dynamic balance, functional mobility, and walking capacity in these CNDs, consistent with prior findings [22,23,25,27,29,30,33,34,35,36]. The digital tools integrated into these TR protocols are specifically selected to support intensive rehabilitation by combining task-oriented and impairment-oriented exercises.

We further hypothesize that TRcA will demonstrate superior benefits compared to TRsA, particularly for secondary outcomes such as physical capacity and functional mobility [40,41]. Based on the existing literature, task-oriented training is known to leverage neuroplasticity to enhance motor functions, including balance and mobility, while impairment-oriented approaches focus on restoring specific skills, such as strength [75].

Another noteworthy feature of TR is its ability to facilitate controlled and personalized exercises in home settings. By incorporating sensory feedback, both visual and auditory, TR actively engages patients, promoting a more interactive and effective rehabilitation experience. Moreover, TR’s flexibility allows patients to schedule rehabilitation sessions according to their daily routines and preferences, further enhancing engagement and adherence to treatment. Previous studies have demonstrated that TR approaches maintain high adherence rates, ensuring continuity of care and yielding both short- and long-term benefits in motor and non-motor functions. These include improved quality of life, greater participation in daily activities, and enhanced autonomy This adaptability is a key determinant of the structural and procedural aspects of digital treatment, playing a crucial role in achieving positive health and quality-of-life outcomes for patients [76].

Despite its benefits, TR poses challenges and limitations, particularly regarding patient unfamiliarity with technology. To mitigate the digital divide—a phenomenon where individuals lack access to or proficiency in digital tools—all participants will receive comprehensive training at the clinical center, with caregivers present where possible. This training will cover device operation, internet connectivity issues, and space optimization for home rehabilitation. Ongoing technical support will further ensure usability and address exercise-related concerns. Moreover, TR systems are expected to demonstrate not only usability but also safety when appropriately prescribed and utilized in rehabilitative care. By addressing these challenges and leveraging technological advancements, TR can provide equitable, effective rehabilitation services, transforming care for individuals with CNDs.

